### Aims and design

The primary aim of our study is to investigate the effect of a smartphone app combined with game elements on the level of physical activity of adults and older adults, measured by the average number of daily steps. The secondary aims are (1) to verify the effects of the intervention on cardiometabolic and cardiovascular health, lung function, and cardiorespiratory fitness; and (2) to verify the relationship between age group and the response rate.

We will conduct a Sequential Multiple Assignment Randomized Trial (SMART). This study was approved by the Ethics Committee of the Federal University of Sao Paulo (# 0499/2018) and is registered in the Brazilian Clinical Trials Registry (RBR-8xtc9c).

The SMART design has been recommended over the classical randomized controlled trial for technology-based interventions [12, 13] as it allows adaptations over time based on the participants’ response to the intervention. Despite the large potential and shown feasibility [14], the SMART design has, thus far, hardly been conducted in smartphone and gamified interventions.

The adaptive intervention protocol will last 6 months. Initially, participants will be randomized into one of three groups (group 1: app + tailored messages; group 2: app + tailored messages + gamification I; control group: physical activity counseling) (Fig. 1). Over 12 weeks, we will record the average number of steps per day for each participant from groups 1 and 2. At 6 weeks from initiation, participants will be classified into responders and non-responders according to the targeted average number of daily steps; all those considered as non-responders will be re-randomized, with the chance to participate in a third group – group 3: app + tailored messages + gamification II (Fig. 1). At the end of the 12 weeks, participants will continue using the app but will no longer receive any direct intervention from investigators. All participants, including those in the control group, will be reassessed at 3 and 6 months from baseline. The protocol timeline is shown in Fig. 2.

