### Interventions

#### Group 1 – App + tailored messages

Participants will use the app to track the number of daily steps and they will receive weekly text messages on their smartphones, with information about their performance on last week and motivational phrases according to their behavior-change status at the end of the protocol, the responders of Group 1 will end up in the subgroup A, while non-responders will end up in the subgroups B or C.

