#### Group 3 – App + tailored messages + gamification II

The second stage of gamification will be available in the protocol by the time of the intermediate assessment (6th week of intervention). Gamification II will include the same features of gamification I, plus opportunities for socialization among participants (biweekly group meetings) and discussion forums about physical activity.

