### Defining responders and non-responders

The American College of Sports Medicine recommendations about the quantity and intensity of physical activity suggest increases of 2000 steps per day to achieve improvements in cardiovascular health [15]. After a pre-test with persons from researchers’ networks using a smartphone app with a pedometer, we observed that the target of increasing 2000 steps/day would not be realistic to our population. Therefore, we decided to plot the average number of steps of participants in a graph using a linear tendency line and participants that present a positive slope, i.e., a tendency to increase step counts, will be considered as responders. Consequently, participants with a zero or negative slope, i.e., a tendency to maintain or decrease step counts, will be considered as non-responders. Additionally, we will use the app’s first-week step count as a reference for both sending the tailored messages and analyzing participants’ slopes. Thus, we believe that this way we will be able to set individualized and feasible goals for our population.

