#### Intermediate assessment

The intermediate assessment to identify responders and non-responders will take place at week 6 from the beginning of the protocol. We will calculate the average number of steps/day from weeks 1 to 6, and compare with the number of steps/day from the initial assessment. Participants identified as non-responders will then be re-randomized and will receive instructions about the new phase of intervention (Fig. 1). We will collect the average number of steps per day using the app interface; all participants will use the app for 1 week after randomization prior to any intervention and we will consider the step count from the first week as a comparator for weekly and intermediate assessments.

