### Data analysis

Participants’ characteristics will be presented by descriptive statistics. We will use ANOVA tests to compare the effect of interventions on the increase of physical activity levels, cardiovascular and metabolic health, lung function, and cardiorespiratory fitness among groups A + B + C and D + E + F pre- and post-intervention compared to the control group. Additionally, we will use the same test to analyze the effect of interventions on the average number of daily steps comparing the final subgroups (A to F) against the control group as well as the subgroups A + F, B + D and C + E against the control group.

To analyze the relationship between age and the response rate to each intervention, we will group responders and non-responders according to age ranges (20–30 years old, 31–40, 41–50, 51–60, 61–70, and 71 and older) and compare them in subgroups from A to F using Pearson or Spearman correlations (according to data distribution).

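### The age-by-response analysis is set in subgroups A to F, but week-6 response defines those subgroups, so it cannot vary within them and says nothing about response to group 3

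*Protocol article*

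**What the plan says.** The second of the two secondary aims (Aims and design) is "to verify the relationship between age group and the response rate". Data analysis turns this into a specific plan. It sets out "To analyze the relationship between age and the response rate to each intervention", sorts responders and non-responders into six age bands, and will "compare them in subgroups from A to F using Pearson or Spearman correlations".

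The rest of the protocol article fixes what response means and when it is known:

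- **Rule** (Defining responders and non-responders): "participants that present a positive slope, i.e., a tendency to increase step counts, will be considered as responders". A zero or negative slope makes a non-responder.
- **Timing** (Intermediate assessment): "The intermediate assessment to identify responders and non-responders will take place at week 6 from the beginning of the protocol".
- **Start of group 3** (Group 3 section): "The second stage of gamification will be available in the protocol by the time of the intermediate assessment (6th week of intervention". Under Aims and design, only people classed as non-responders are re-randomised, with a chance of entering it.
- **Subgroups** (Group 1 section): "the responders of Group 1 will end up in the subgroup A, while non-responders will end up in the subgroups B or C". The Group 2 section does the same with D for responders and E or F for non-responders.
- **Second-stage treatments** (Sample size): B is the switch to group 2, E the switch to group 1, and C and F the switches to group 3.

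App step recording does not stop at week 6: "Over 12 weeks, we will record the average number of steps per day for each participant from groups 1 and 2". No section uses the later counts to classify response again.

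**The concern.** The planned analysis asks for a response rate for each intervention and uses the final subgroups as its units. Those subgroups are built from the response status itself. The analysis therefore conditions on the variable it wants to relate to age.

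Two things follow. First, response has no variation inside any of the six subgroups, so the correlation named there has nothing to work on. Second, people in B, C, E and F carry a label earned under the treatment they were moved away from. If that label is tabulated against the treatment they were moved to, group 3 shows no responders in any age band, purely by definition. A reader could take this as a failure of gamification II at all ages. Secondary aim 2 would be reported with an artefact for one of the three app interventions.

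**Working it through.** **Inputs (Sample size section).** 42 participants, 14 per arm, so 2 × 14 = 28 in the two app arms. Planned non-response q = 50%, range 35–65%. At least m = 3 people in each of B, C, E and F, with probability k of about 80–90%.

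**Step 1: the plan's own figure.** Suppose the non-responders of one app arm are split evenly. Two subgroups of at least 3 then need at least 6 non-responders among 14. With X ~ Binomial(14, 0.5):

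P(X ≥ 6) = 1 − (1 + 14 + 91 + 364 + 1001 + 2002)/2^14 = 1 − 3473/16384 = 0.788.

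That is close to the lower end of k, so 14 per arm reproduces for a single arm. The sample size is not in dispute here. It confirms that q is the week-6 non-response rate within an app arm, and that is how it is used below.

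**Step 2: response within each subgroup under the stated rule.**

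| Subgroup | Initial arm | Week-6 status | Treatment after week 6 | Share of responders, any age |
|---|---|---|---|---|
| A | Group 1 | Responder | Group 1 | 100% |
| B | Group 1 | Non-responder | Group 2 | 0% |
| C | Group 1 | Non-responder | Group 3 | 0% |
| D | Group 2 | Responder | Group 2 | 100% |
| E | Group 2 | Non-responder | Group 1 | 0% |
| F | Group 2 | Non-responder | Group 3 | 0% |

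A Pearson or Spearman coefficient divides by the standard deviation of each variable (of its ranks, for Spearman). Inside any row the standard deviation of response is 0, so the coefficient is 0/0 and undefined. Pooling all six rows restores variation, but the result is then no longer specific to an intervention.

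**Step 3: who has no status for the treatment they are on.** This is everyone in B, C, E and F, or 28q. Those in group 3 (C + F) number 28q/2 if re-randomisation is 1:1. The protocol article does not state the ratio, so this is an assumption. Everyone is taken to reach week 6.

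| q | B+C+E+F = 28q | Share of 28 | C+F = 28q/2 | Share of 28 |
|---|---|---|---|---|
| 35% | 9.8 | 35% | 4.9 | 17.5% |
| 50% | 14 | 50% | 7 | 25% |
| 65% | 18.2 | 65% | 9.1 | 32.5% |

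**Step 4: what can be analysed.** Taken by initial arm, week-6 status does vary. A against B+C gives response to group 1, and D against E+F gives response to group 2, with 14 people in each arm. Age can be related to response there.

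**The case against.** The strongest reply is that response in this design is a tailoring status. It decides who is re-randomised, so scoring it only at the decision point is coherent. The aim itself mentions only the response rate, and the Sample size section ties non-response to the end of the sixth week. On that reading, the interventions meant are groups 1 and 2, all 28 app participants have a score, and the letters A to F merely encode initial arm and week-6 status.

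Much of this stands. Aim 2 is answerable for groups 1 and 2. The reply does not rescue the text as written, however. Data analysis uses the pooled sets A+B+C and D+E+F for the ANOVA but names A to F for the age analysis. It also speaks of each intervention, when there are three app interventions. Nor is this a detail left to an analysis plan: the quantity, the units and the test are all stated, and together they fail.

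Four stronger readings might be inferred, and the documents do not support them:

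- *Group 3 has no endpoint.* Data analysis compares daily steps in every final subgroup, including C and F, with control. Accelerometer steps are also measured at 3 and 6 months.
- *Second-stage response cannot be scored at all.* App steps are recorded over 12 weeks. What is missing is a rule and a window, not data.
- *About half of the app participants are unscored.* Each has a week-6 score, but for the earlier treatment. Group 3 alone is about a quarter.
- *Planning of the later trial suffers.* The Sample size section plans that trial from the variation in steps, up to 40% loss and 65% non-response. It uses no second-stage response rate.

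**Conclusion.** The point holds for one secondary analysis. Followed as written, the age-response comparison in subgroups A to F is degenerate: response is 100% in A and D and 0% in B, C, E and F at every age. The 0% in C and F carries no information about gamification II.

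At q = 50%, 14 of 28 app participants have only a status for the treatment they left (9.8 to 18.2 over 35–65%). About 7 of these are in group 3 (4.9 to 9.1). The first count rests on the plan's own q and on all 28 reaching week 6; the second also rests on 1:1 re-randomisation.

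The evaluation of group 3 on mean daily steps and the sample size are untouched. The correction is worth making because it is cheap and prevents a definitional zero from being read as a result.

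**What to change.** **Core change, in Data analysis.** Relate age to week-6 response by initial arm: A+B+C for group 1 and D+E+F for group 2. Drop subgroups A to F as the units of this analysis.

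**For group 3 and the switches into groups 1 and 2, choose one of two statements:**

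1. No response rate is estimated for second-stage treatments.
2. A descriptive week-12 response is derived from app steps recorded after re-randomisation. Its reference period (the first app week, or the weeks around re-randomisation) is named in advance, because the choice can change a person's status. It triggers no further re-randomisation.

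If the second option is taken, the text should add that these rates:

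- apply only to first-stage non-responders;
- rest on few people: about 7 in group 3, or 7/6 ≈ 1.2 per age band;
- may reflect regression to the mean, since these people were selected for a flat or falling slope;
- are not comparable with the week-6 rates.

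**Cost.** The core change is a rewording. The second option adds one small calculation on step counts already planned to week 12, with no new visit or measurement. Its downside is that the second-stage rates will be imprecise and can only be described.

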### Sample size

The main objective of a SMART study relies on the feasibility of carrying out a future large-scale trial, rather than investigating the effects of the proposed set of treatments. To reach this goal, we must ensure that the number of subjects will be sufficient and balanced among all of the subgroups. According to Almirall et al. [16], a fixed probability *k* of about 80–90% should be considered so that at least *m* participants would end in non-responders’ subgroups B, C, E and F (Fig. 1). Considering a range of non-response rates in SMART studies of 35–65%, we calculated an *m* of 3 participants per subgroup as sufficient to ensure familiarity with the protocol, treatment delivery, and identification of potential problems. For a non-response rate of q = 50% at the end of the 6th week, our pilot SMART study will require 42 participants (14 per arm) [16].

After conducting this SMART pilot, we will consider the variation on the average number of steps per day to calculate the sample size of the trial, including an up to 40% loss to follow-up and a less optimistic non-response rate of 65%. To increase the feasibility of a future large-scale trial, we will calculate the sample size considering groups A + B (maintain – switch to group 2), groups A + C (maintain – switch to group 3), groups D + E (maintain – switch to group 1), groups D + F (maintain – switch to group 3), and the control group.

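### The age-and-response analysis uses the step trend only as yes/no and age only as six bands; a rank analysis of the uncut values in the 28 app users would be more sensitive and needs no new data

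*Protocol article*

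**What the plan says.** Under Aims and design, the second secondary aim is "to verify the relationship between age group and the response rate".

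Under Defining responders and non-responders, a straight line is fitted to each participant's step averages, and "participants that present a positive slope, i.e., a tendency to increase step counts, will be considered as responders"; a flat or falling line makes a non-responder. Under Intermediate assessment, this status decides at week 6 who is re-randomised. That section describes the comparison as the weeks 1 to 6 average against the first-week count. Either description yields a number before it yields a class. Age is recorded at baseline under Demographic and socioeconomic information.

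Under Data analysis, "we will group responders and non-responders according to age ranges (20–30 years old, 31–40, 41–50, 51–60, 61–70, and 71 and older"; these groups are then compared in subgroups A to F by Pearson or Spearman correlation, the choice depending on the data distribution. No analysis of the uncut slope or uncut age is described for this aim.

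On numbers, "our pilot SMART study will require 42 participants (14 per arm". Only the app arms can be classified, because "we will record the average number of steps per day for each participant from groups 1 and 2". The planning assumption reads "For a non-response rate of q = 50% at the end of the 6th week".

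**The concern.** The yes/no cut has a job at week 6: it triggers re-randomisation. It does not follow that the age analysis must use only the cut version. The cut is at zero slope, chosen after the protocol set aside a 2000-step increase as unrealistic, so a very small rise counts the same as a very large one. People with nearly flat lines are sorted largely by week-to-week noise. Age is coarsened as well: 28 / 6 is about 4.7 people per band.

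With so few people, an age gradient that the collected data could show is more likely to be missed on the cut scales. That matters because age and response is one of the two stated secondary aims.

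**Working it through.** **Inputs from the protocol article.** 14 per arm and two app arms, so n = 28; non-response q = 50% for planning, with a range of 35% to 65%; m = 3 per non-responder subgroup; response = slope above zero; six age bands.

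**Inputs assumed, because the article gives none.** Two-sided 5% level; correlation of age with slope of 0.3 to 0.5 (0.2 and 0.6 also tried); age uniform over 20 to 80; slope linear in age with normal errors, then with heavy-tailed errors.

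**The plan's own figure first.** Three people in each of two re-randomised subgroups need at least 2 × 3 = 6 non-responders in an arm. With 14 per arm and q = 0.5:

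P(X ≥ 6) = 1 − (1 + 14 + 91 + 364 + 1001 + 2002)/16384 = 1 − 3473/16384 = 0.788.

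This is close to the lower end of the stated 80–90%, so 14 per arm reproduces on a single-arm reading. It was set by subgroup counts. No power is stated for secondary aim 2.

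**Where the loss arises.** Splitting a normal variable at its median multiplies a correlation by √(2/π) = 0.80. Cutting uniform age into six roughly equal bands multiplies it by about √(1 − 1/36) ≈ 0.98 to 0.99. So a true 0.5 becomes about 0.5 × 0.80 × 0.98 = 0.39. The Fisher-z approximation, Φ(√(n−3)·atanh ρ − 1.96), gives Φ(5 × 0.549 − 1.96) = 78% uncut and Φ(5 × 0.413 − 1.96) = 54% cut. It is rough at this n, but it shows that the slope cut does the damage.

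**Simulation.** 20,000 trials per setting, n = 28, q = 50%, all app users pooled, t-test of the correlation, normal errors. Rejection was about 5% at zero correlation.

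| Correlation | Spearman, age in years vs slope | Spearman, band vs yes/no | Loss (points) | Pearson, uncut vs cut |
|---|---|---|---|---|
| 0.3 | 33% | 24% | 9 | 35% vs 24% |
| 0.4 | 55% | 40% | 15 | 58% vs 41% |
| 0.5 | 77% | 60% | 17 | 81% vs 61% |

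**Sensitivity.**
- Split of the loss at 0.5 (Pearson): banding age alone takes 81% to 80%; cutting slope alone takes 81% to 62%.
- Normal or younger-skewed ages: Spearman loss about 8 to 19 points at 0.3 to 0.5.
- q = 35% or 65%: Spearman loss up to about 21 points at 0.5.
- One arm of 14 at 0.5: Spearman 43% vs 32%.
- Correlation 0.2: loss of about 4 points.
- Heavy-tailed errors scaled to the normal interquartile range, coefficient 0.5. With t on 3 df: Spearman uncut 67%, cut scales 60%, Pearson uncut about 58%. With t on 2 df: 63%, 60% and 44%. Over coefficients 0.3 to 0.5 the Spearman gain is about 1 to 7 points.

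**The case against.** **The aim is worded as age group against response rate.** This stands. Which ages fail to respond is a fair question where failure triggers re-randomisation, and age against size of slope is a different question. A reader might infer that the response-rate analysis should be replaced or made descriptive only. The documents do not support that; the case is for an addition.

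**The gain depends on well-behaved slopes.** This also stands. The Discussion reports that many pre-test participants did not use the phone during outdoor activity, so outlying slopes are plausible. With heavy tails an ordinary regression or Pearson correlation of slope on age loses its advantage and can do worse than the cut version. A rank method keeps a gain, but a small one.

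**The pooled comparison is not literally the plan.** Correct. The Interventions section places only responders in A and D, and only non-responders in B, C, E and F. Response is therefore constant within each subgroup, and no correlation of age with response can be computed there. Pooling is the more favourable reading of the sentence, and the loss remains under it.

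**Raw slope may reflect starting volume.** If older users walk less at first and improve by the same percentage, raw slope can vary with age while response rate does not. This has to be handled in the added analysis.

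**It is a feasibility pilot.** True, and no later sample size is given, so the figures apply to the pilot alone. Nothing in the article says that a null result would be taken as showing no age dependence.

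**Conclusion.** The point holds in limited form. The uncut slope and age are available, the Data analysis section uses neither for secondary aim 2, and in 28 pooled app users this costs about 9 to 17 points of power against Spearman at correlations of 0.3 to 0.5. That rests on assumed normal errors, uniform ages, q = 50% and a 5% level. With heavy-tailed slopes the cost is about 1 to 7 points.

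Two stronger readings are not supported. One is that the six age bands are the main fault: they cost about 1 to 2 points in the base case. The other is that the change would make the pilot adequate for this aim: power stays near 33% to 55% at correlations of 0.3 to 0.4. This is an inexpensive improvement to a secondary analysis.

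**What to change.** In Data analysis:

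1. Add a prespecified rank-based (Spearman) analysis of each app user's week 1 to 6 step slope against age in years. Include everyone first randomised to groups 1 and 2, adjust for or stratify by first-stage group, and adjust for or scale by the first-week step count. Name it as the more sensitive test of an age gradient.
2. Keep the analysis of response rate by age as the stated aim, but run it over all users in each first-stage group with age in years, not within subgroups A to F. The six bands can remain as a table.
3. Leave the responder cut unchanged for re-randomisation.

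The cost is two or three sentences, with no new data or participants. The downside is that the added result describes a trend in the size of the slope and not a response rate, so the two results need to be reported side by side and may differ.

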#### Group 2 – App + tailored messages + gamification I

Additionally to monitoring the number of steps and individual messages, participants will be encouraged to join virtual challenges; for each challenge they complete, a virtual badge will be given. The challenges available will be related to the target number of steps per day, target distance walked in the month, and group competitions where the total number of steps is compared among the different groups of app users. Further, there will be rankings of the number of steps among all users at the end of the protocol, the responders of Group 2 will end up in the subgroup D, while non-responders will end up in the subgroups E or F.

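### The age-by-response analysis uses subgroups A to F as its unit, but response defines those subgroups; it should be run by first-stage arm

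*Protocol article*

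**What the plan says.** The second secondary aim in Aims and design is "to verify the relationship between age group and the response rate". Data analysis gives one method for it: "To analyze the relationship between age and the response rate to each intervention, we will group responders and non-responders according to age ranges", using six bands from 20–30 to 71 and older, and then "compare them in subgroups from A to F using Pearson or Spearman correlations (according to data distribution".

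Four other sections fix what response and the subgroups are.

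- **Response is binary.** Under Defining responders and non-responders, a positive slope makes a responder, and "participants with a zero or negative slope, i.e., a tendency to maintain or decrease step counts, will be considered as non-responders".
- **It is classified once.** Under Intermediate assessment, "The intermediate assessment to identify responders and non-responders will take place at week 6 from the beginning of the protocol". No later classification is defined.
- **It determines the subgroup.** For group 1, "the responders of Group 1 will end up in the subgroup A, while non-responders will end up in the subgroups B or C". For group 2, "the responders of Group 2 will end up in the subgroup D, while non-responders will end up in the subgroups E or F".
- **Sample size confirms the labels.** It describes B, C, E and F as the places where non-responders end up: "participants would end in non-responders’ subgroups B, C, E and F (Fig. 1".

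**The concern.** The subgroups are built from the outcome under study. Asking how response varies with age inside a group selected on response is asking how a constant varies. The B/C and E/F splits add a second difficulty: they come from the re-randomization, which follows the week-6 classification, so they cannot bear on who responded by week 6.

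At stake is the only analysis the article gives for this aim. If it is run subgroup by subgroup, the software returns no coefficient, and the analyst must choose a substitute with the data in view. Some substitutes would give a number that answers a different question. The primary comparison is not touched.

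**Working it through.** The protocol states no figure to reproduce here. The check is structural, with the pilot's numbers as illustration.

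**Inputs.** Let y = 1 for a responder and 0 for a non-responder (Defining responders and non-responders). Subgroup membership is as described under Group 1 and Group 2. Sample size gives 14 per arm and an assumed non-response rate q = 50%, within a range of 35–65%.

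**Step 1: response inside each subgroup.**

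| Subgroup | First-stage arm | y for every member | Response rate | Expected n at q = 50% |
|---|---|---|---|---|
| A | Group 1 | 1 | 100% | 14 × 0.5 = 7 |
| B, C | Group 1 | 0 | 0% | 14 × 0.5 / 2 = 3.5 each |
| D | Group 2 | 1 | 100% | 7 |
| E, F | Group 2 | 0 | 0% | 3.5 each |

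**Step 2: the coefficient.** Pearson's r = cov(age, y) / (SD of age × SD of y). With y constant, the covariance is 0 and the SD of y is 0, so r = 0/0. Spearman fails the same way, because all values of y are tied and their ranks have no variance. Replacing age by its band changes nothing: the response rate is the same in every non-empty band of a subgroup. None of this depends on the number of participants.

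A simulation of the stated allocation (14 per app arm, q = 50%, non-responders split evenly between their two subgroups) agrees. Of 2,000 trials × 6 = 12,000 subgroups, none had non-zero response variance.

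**Step 3: by first-stage arm.** A+B+C is everyone randomized to group 1, and D+E+F everyone randomized to group 2. At q = 50% the variance of y in an arm is about 0.5 × 0.5 = 0.25, so both coefficients exist. They fail only if all 14 in an arm share one status, which has probability 2 × 0.5^14 = 0.00012. At either end of the 35–65% range it is 0.65^14 + 0.35^14 = 0.0024. In the simulation, response varied in 4,000 of 4,000 arms.

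**Step 4: precision at pilot size.** The protocol states no alpha or power for this aim, so I assume two-sided 0.05 and 80%. By the Fisher z approximation (rough for a binary outcome), the smallest detectable |r| is tanh[(1.960 + 0.842) / √(n − 3)]:

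- one arm, n = 14: tanh(2.802 / √11) = tanh(0.845) = 0.69
- both arms, n = 28: tanh(2.802 / √25) = tanh(0.560) = 0.51

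At q = 50%, 28 × 0.5 = 14 responders are expected across the two app arms. That is few for a model with age, arm and their interaction.

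**Step 5: other readings of the sentence.**

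- *Head-counts against age band inside a subgroup.* Computable, but this describes the subgroup's age mix, not a response rate.
- *Age against the labels A to F.* This treats an unordered category as a scale.
- *Age against step change or slope inside a subgroup.* Computable, but the sentence names response rate and responder status.
- *One correlation over all of A to F, using the label only to read off who responded.* Computable, but it gives a single coefficient with groups 1 and 2 mixed.

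**The case against.** The strongest reply is that the sentence does not say within each subgroup. It compares responders with non-responders, and no single subgroup contains both, so it may mean across the range A to F, with A and D supplying the responders and the other four the non-responders. A correlation then exists. This stands in part: the reading is possible, and it rules out the claim that the analysis cannot be computed under any reading. It does not rescue the plan, because the text does not state it and the sentence asks about response to each intervention, which one pooled coefficient does not give.

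Three stronger criticisms are tempting but not supported.

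- *Six bands by six subgroups make 36 cells for 28 app-arm participants.* A correlation does not need every cell filled. The 28 belong to the pilot, and Data analysis does not confine this analysis to the pilot. The zero-variance point holds at any size and gains nothing from the count.
- *Banding age is an error.* The stated aim is about age group, so banding fits it, and Spearman accepts ordered bands.
- *This is detail that belongs in an analysis plan.* The point is not an omission: the article names a method and a unit, and the unit is the wrong one.

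It is also fair to say that the aim is secondary and that Sample size puts feasibility ahead of effects. That limits the weight of the point but does not remove it.

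**Conclusion.** The point holds in a bounded form. On the within-subgroup reading, the planned correlation is undefined in all six subgroups. On the pooled reading it exists but does not answer the question by intervention. Either way, A to F is the wrong unit.

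The conclusion rests on two things the article states: response is binary and set once at week 6, and it determines subgroup membership. It would change only if a second-stage response (weeks 6 to 12) were defined, since that could vary inside subgroups; the article defines none.

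A reader might infer that the second secondary aim cannot be met. The documents do not support that: age and week-6 status are both planned for collection, and analysing by first-stage arm meets the aim for groups 1 and 2. Precision is a separate limit. At pilot size, under the assumed alpha and power, only correlations of about 0.5 (both arms) to 0.7 (one arm) would be reliably detected, so estimates with intervals matter more than tests. The sentence should be changed, but nothing here affects the primary aim.

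**What to change.** In Data analysis, replace the A-to-F unit with the first-stage arm: A+B+C for group 1 and D+E+F for group 2, groupings the same section already uses for the ANOVA. One suitable form is:

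- **Main analysis.** One logistic regression of week-6 response (yes/no) on age, adjusted for first-stage arm, in all participants of groups 1 and 2. Use Firth or exact estimation if the data are sparse. Report the odds ratio for age with its 95% CI. Do not tie the sentence to 28 participants, so that it also serves the later trial.
- **Age by arm.** This model gives one age effect common to both arms. Arm-specific age effects, through an age × arm term, should be labelled exploratory because they will be imprecise at pilot size.
- **Age bands.** Keep the six bands for a descriptive table of response rates by arm.
- **Scope.** State that the analysis covers response to groups 1 and 2 only. Group 3 begins after the week-6 classification, and no second-stage response is defined for it.

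The smallest acceptable edit is to keep the planned correlation but compute it separately in A+B+C and in D+E+F.

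The cost is a few sentences. The data needed are already planned for collection, and recruitment was still open at the version shown, so the change could be made before analysis.
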